# - Background

Gonioscopy is a vital part of the ophthalmologic examination, as it allows clinicians to evaluate the iridocorneal angle of the eye. The iridocorneal angle contains the orifice to the draining pathway of the aqueous humor from the anterior chamber into the canal of Schlemm. More acute, or “narrow,” angles can put patients at risk for glaucoma due to obstruction of the route of the fluid into the trabecular meshwork. Accumulation of pigment or inflammatory cells can also lead to obstructions of the drainage system and consequent increase in intraocular pressure. Gonioscopy allows clinicians to assess the width of the angle as well as look for any structural deformation or accumulation of material.

The goniolens is a specially designed lens to allow visualization of the angle that is placed on the patient’s cornea by the clinician during the ocular examination. When used in conjunction with a slit lamp, it gives the clinician a view of the iridocorneal angle, which is otherwise masked by the ocular configuration. Although it is considered the gold standard for assessment of the iridocorneal angle, gonioscopy can be difficult to perform. [1] The evaluation of the width of the iridocorneal angle is subjective and requires clinical experience. [1] As such, there is some inter-operator variability in the results obtained using this method.

Due to the time and skill required to obtain an accurate gonioscopic image on a conventional slit lamp, there has been interest in developing alternative methods to obtain quick, accurate, and reliable images of the iridocorneal angle. These alternative methods have involved the use of both new and existing technologies. For instance, currently available 3D Corneal and Anterior Segment Optical Coherence Tomography (3D CAS-OCT) has been used for this purpose. A study investigating the utility of 3D CAS-OCT in evaluating anterior segment parameters found a high degree of intra-grader repeatability, inter-grader repeatability, and correlation with conventional gonioscopy. [2]

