With the goal of someday replacing conventional gonioscopy, a number of imaging devices have been developed specifically to assess anterior segment parameters. The Pentacam-Scheimpflug camera uses the Scheimpflug optical principle to photograph parts of the anterior segment that are not directly in line with the camera’s aperture. [3] The camera takes up to 50 slit images of the anterior segment in 2 seconds and uses software to construct a 3D image. [3] The benefit of this technology is that it requires little operator experience and begins scanning automatically once proper alignment has been achieved. [3] However, Pentacam-Scheimpflug only quantitatively estimates the width of the angle and does not directly visualize it. [3] It therefore cannot be used as a replacement for conventional gonioscopy.

Orbscan Scanning-Slit Topography is a technology that scans the entire surface of the cornea, the iris, and the lens using a slit-scanning beam. [3] By mapping both the posterior

surface of the cornea and the iris, Orbscan calculates an estimation of the iridocorneal angle. [3] However, like Pentacam-Scheimpflug, it does not directly visualize the angle. Paradigm P60 ultrasound biomicroscope can obtain images of the iridocorneal angle and has been used for decades in the form of A- and B-scans. [3] However, in order to obtain an image, it requires direct contact with the eye, which is uncomfortable for the patient, and is highly operator- dependent. [3]

The clinical utility of an imaging device that can produce quick, accurate, and reliable images of the iridocorneal angle is clear. If the NIDEK Gonioscope GS-1 can produce images that are of comparable quality to digital images obtained from a goniolens and slit lamp, it has the potential to increase the speed of clinical examination in glaucoma clinics and improve workflow by replacing conventional gonioscopy.

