# Primary Outcome Variables

Images obtained by the NIDEK Gonioscope GS-1 will be compared with ultrasound biomicroscopy images and digital gonioscopic images obtained using a goniolens and slit lamp to determine if the NIDEK Gonioscope GS-1 can accurately and reliably capture relevant findings. To determine the accuracy of the NIDEK Gonioscope GS-1, we will use ANOVA to determine if the iridocorneal angle measurements obtained from the NIDEK Gonioscope GS-1 are statistically similar to measurements obtained from ultrasound biomicroscopy and standard gonioscopy. To determine inter-observer reproducibility when using this device, two observers will examine each image obtained from NIDEK Gonioscope GS-1 and separately determine the iridocorneal angle. Inter-observer reproducibility will be determined using Kappa's statistics and intraclass correlation coefficient. Lastly, we will determine if the time it takes to obtain images from the NIDEK Gonioscope GS-1 is statistically different from the time it takes to obtain images by conventional gonioscopy. This will be done via ANOVA.

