# - Methods

# Study Procedure

Subjects who meet eligibility criteria will be identified by study team and will be consented for the study. During their usual ophthalmology visit, all subjects will undergo conventional gonioscopy, ultrasound biomicroscopy, and gonioscopy with NIDEK Gonioscope GS-1. The NIDEK Gonioscope GS-1 will only be used on patients who are in the study. The experimental part of the visit using the NIDEK Gonioscope GS-1 should take approximately 10 minutes,

For conventional gonioscopy, the clinician may obtain digital images of the iridocorneal angle using a slit lamp and goniolens. For ultrasound biomicroscopy, the clinician may obtain ultrasound images that will then be stored within the biomicroscope device. For gonioscopy with NIDEK Gonioscope GS-1, the device may obtain and store images of the iridocorneal angle.

Following collection of the images, one ophthalmologist may examine images obtained from conventional gonioscopy and determine the width of the iridocorneal angle. The same ophthalmologist will determine the width of the iridocorneal angle from the ultrasound biomicroscopy images. This ophthalmologist will be masked to patient names and diagnoses. A second and potentially third ophthalmologists may examine images obtained from NIDEK Gonioscope GS-1 and determine the width of the iridocorneal angle. These ophthalmologists will also be masked to patient names and diagnoses.

Statistical analysis will be performed to determine the association between the findings of iridocorneal angle width in conventional gonioscopy images, ultrasound biomicroscopy images, and NIDEK Gonioscope GS-1 images of each patient. Further statistical analysis will be performed to determine the inter-observer repeatability of the findings of the two ophthalmologists who examined the images from NIDEK Gonioscope GS-1.

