# Primary Analyses

The analysis of the width of the iridocorneal angle will be done according to both the Scheie and Shaffer grading systems. Relationships between results obtained from conventional gonioscopy, ultrasound biomicroscopy, and NIDEK Gonioscope GS-1 will be evaluated by linear and quadratic models, as well as more advanced statistical methods.

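### If run as one three-level test, the accuracy ANOVA can turn on a gap between ultrasound biomicroscopy and gonioscopy, and its result does not show whether GS-1 departs from gonioscopy

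*Protocol*

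**What the plan says.** For accuracy, Primary Outcome Variables (4.2 in the table of contents) gives one method and one question: "To determine the accuracy of the NIDEK Gonioscope GS-1, we will use ANOVA to determine if the iridocorneal angle measurements" from GS-1 are "statistically similar to measurements obtained from ultrasound biomicroscopy and standard gonioscopy". It does not say how many ANOVAs will be run, names no contrast, and does not say which reference carries the conclusion.

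Three other places bear on the reading:

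- Study Procedure makes the comparison paired: "all subjects will undergo conventional gonioscopy, ultrasound biomicroscopy, and gonioscopy with NIDEK Gonioscope GS-1".
- Background does not give the two references equal standing. Of conventional gonioscopy it says that "it is considered the gold standard for assessment of the iridocorneal angle", and the benefit it hopes for is to "improve workflow by replacing conventional gonioscopy".
- Primary Analyses adds that relationships between the three sets of results "will be evaluated by linear and quadratic models, as well as more advanced statistical methods". It too names no contrast and no lead reference.

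**The concern.** With three modalities under one ANOVA, the null hypothesis is mean(GS-1) = mean(UBM) = mean(gonioscopy). One part of this, mean(UBM) = mean(gonioscopy), has nothing to do with the new device. The protocol gives no reason to expect it to hold: Background describes gonioscopy as a subjective view that varies between operators, and Potential Risks describes UBM as an ultrasound image taken through a water-filled balloon.

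If the two references differ on average, no device can have the same mean as both, and with enough eyes the test will reject. The F-statistic does not show whether GS-1 departs from gonioscopy, from UBM, or lies between them. So the stated accuracy test does not isolate the comparison that matters most for replacing gonioscopy.

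**Working it through.** **What the protocol supplies.** Its sample size is set for kappa: 94 evaluable eyes, raised to 120 for 10–20% uninterpretable images (94/0.8 = 117.5, so 120 covers it). It gives no power figure for the ANOVA, so there is no stated figure to reproduce. I use 94 eyes as the working size.

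**What has to be assumed.** The SD, the within-eye correlation between modalities and the mean gap between UBM and gonioscopy are not in the protocol. I take SD 1, a common correlation ρ of 0.3 to 0.7, gaps d of 0.2, 0.3 and 0.5 SD, normal measurements, and eyes treated as independent.

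**Formula.** For a repeated-measures ANOVA with three levels and n eyes, the F-statistic has 2 and 2(n − 1) degrees of freedom and noncentrality λ = n × Σ(μⱼ − μ̄)² / (1 − ρ). At n = 94 the degrees of freedom are 2 and 186, and the 5% critical value is 3.04.

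**Case 1: GS-1 and gonioscopy equal, UBM shifted by d.** The means are 0, 0, d, so Σ(μⱼ − μ̄)² = 2d²/3. For d = 0.3 this is 0.06 and n × 0.06 = 5.64. Then λ = 5.64/0.7 = 8.06 at ρ = 0.3, 5.64/0.5 = 11.28 at ρ = 0.5, and 5.64/0.3 = 18.8 at ρ = 0.7. Probability that the ANOVA is significant:

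| UBM shift | ρ = 0.3 | ρ = 0.5 | ρ = 0.7 |
|---|---|---|---|
| 0.2 SD | 37% | 50% | 73% |
| 0.3 SD | 71% | 86% | 98% |
| 0.5 SD | 99% | 99.9% | 100% |

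With no shift the rate is 5%. Simulation agrees with the formula. An ordinary one-way ANOVA that ignores the pairing rejects less often, in about 48–54% of simulated trials at 0.3 SD.

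The paired contrasts in the same simulated trials show where the signal comes from. At d = 0.3 and ρ = 0.5, GS-1 versus gonioscopy rejects in about 5% and GS-1 versus UBM in about 82%. At ρ = 0.7 the figures are about 5% and 96%. The ANOVA is picking up a real difference from UBM, but it does not report it as such.

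**Case 2: GS-1 midway between the references.** The means are 0 for GS-1, −d/2 for gonioscopy and d/2 for UBM, so Σ(μⱼ − μ̄)² = d²/2. For d = 0.3 this is 0.045 and n × 0.045 = 4.23. Then λ = 6.04, 8.46 and 14.1 for ρ = 0.3, 0.5 and 0.7, and the ANOVA is significant in 58%, 74% and 93% of trials. At ρ = 0.5 each GS-1 contrast taken alone is significant in only about 30%. In roughly 14–19% of simulated trials, across the three correlations, the ANOVA is significant while neither GS-1 contrast is. In those trials the gap between the comparators decides the result.

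**The case against.** Several points on the other side are sound.

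- **The text does not say one ANOVA.** It gives no number of tests and no rule that a significant F means GS-1 has failed. The same section uses ANOVA for imaging time, a comparison of two modalities ("This will be done via ANOVA"), so the word alone does not imply a three-level test. Follow-up contrasts are often left to a statistical analysis plan, which is not at hand. What stands against this is that the accuracy sentence names three modalities under one method, and that no other criterion for similarity is offered.
- **A reader might infer that a sound device is failed because of the comparators alone.** The documents do not support that. If GS-1 equals gonioscopy and UBM differs, GS-1 differs from UBM by the same amount. The objective names both references, so finding GS-1 not similar to both would then be correct; it misleads only about gonioscopy.
- **A reader might also infer that the replacement question goes unanswered.** That is too strong. Number of Participants bases the sample size on kappa between manual gonioscopy and GS-1, a direct comparison, and Study Procedure and Primary Analyses plan further work on how the modalities relate.
- **The size of the effect is assumed.** The protocol grades angle width by the Scheie and Shaffer systems, whereas the calculation uses normal values. One ophthalmologist reads both the gonioscopy and the UBM images while others read GS-1, which may pull the two references together. Nothing in the protocol shows that UBM is the outlier.

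**Conclusion.** The point holds conditionally. If the accuracy analysis is a three-level ANOVA, a gap between UBM and gonioscopy can drive a significant result, and that result does not show whether GS-1 departs from gonioscopy. At 94 eyes, with GS-1 equal to gonioscopy, the chance of such a result runs from about 37% (0.2 SD shift, correlation 0.3) to nearly 100% (0.5 SD shift). This is a matter of power, not a certainty.

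The percentages rest on the assumed SD, correlation, gap and normality, and on treating eyes as independent. Two eyes per patient would change the effective sample size but not the direction. That the F-test cannot identify which pair differs needs none of these assumptions. It should be corrected, because the better method is simple and uses data already planned.

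**What to change.** In Primary Outcome Variables, replace the ANOVA as the accuracy criterion by separate within-eye contrasts: GS-1 minus conventional gonioscopy, and GS-1 minus UBM. Give each its own estimate and confidence interval, with clustering on patient because most patients contribute both eyes. Report gonioscopy minus UBM beside them as a benchmark for how far the two references differ from each other.

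If the sponsor agrees that gonioscopy is the reference to be replaced, name GS-1 minus gonioscopy as the lead contrast. This ranking is optional; the separate contrasts are useful without it.

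The cost is a short change of wording and no new data. The downsides are two comparisons in place of one test and, if a lead contrast is named, UBM becoming the secondary reference in an objective that now names both jointly. The absence of a similarity margin is a separate matter that this change does not settle.

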# - Study Design

# Number of Study Sites

This study will take place at the New York University Langone Health Department of Ophthalmology and Bellevue Hospital.

# Study Population

This study will enroll patients that have been diagnosed with glaucoma or who are glaucoma suspect.

# Number of Participants

Following a preliminary data collection, we were able to estimate the sample size needed to reach statistically significant results. Assuming that the manual gonioscopy and automated gonioscopy GS-1 have an equal probability of recording a diagnosis, Cohen's Kappa of 0.34 was measured. To detect a fair agreement between the two modalities, while achieving 80% power and 5% type I error, we will need to collect data from 94 eyes. To account for the portion of images that are uninterpretable due to poor quality (10-20%), we asses a total of 120 eyes (60 participants) would be satisfactory for us to estimate the GS-1 as a diagnostic tool accurately.

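### The 80% power is claimed for a kappa between gonioscopy and GS-1 that no named analysis uses, and the 94 eyes cannot be verified from the inputs given

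*Protocol*

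**What the plan says.** Protocol 5.3 (Number of Participants) reports that preliminary data were used for sizing. Assuming that the manual and automated methods "have an equal probability of recording a diagnosis, Cohen's Kappa of 0.34 was measured". It then sets the aim and the error rates, "To detect a fair agreement between the two modalities, while achieving 80% power and 5% type I error", and arrives at 94 eyes. An allowance of 10–20% for uninterpretable images brings the target to 120 eyes from 60 participants.

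Section 4.2 (Primary Outcome Variables) assigns the methods. Accuracy, meaning GS-1 against ultrasound biomicroscopy and standard gonioscopy, is to be judged by ANOVA on angle measurements. Kappa appears for a different comparison, the two readers of the same GS-1 image: "Inter-observer reproducibility will be determined using Kappa's statistics and intraclass correlation coefficient".

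Section 6.7 (Primary Analyses) grades angle width by Scheie and Shaffer and says that relationships between the three modalities "will be evaluated by linear and quadratic models", followed by an open reference to more advanced methods. The Study Procedure text in section 6 speaks only of association between modalities.

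**The concern.** A sample-size statement is useful only if a reader can see which analysis it powers and under which hypothesis. Here both are in doubt.

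First, the sized quantity is a chance-corrected agreement between two modalities on recording a diagnosis. The analyses named for that comparison are ANOVA and regression on angle width. Both the endpoint and the statistic differ, and kappa is given to another comparison.

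Second, the calculation gives a single kappa, 0.34, without saying whether it is the null or the alternative. Excluding chance agreement, showing agreement above a floor, and showing improvement on the pilot value are different claims that need very different numbers of eyes. Section 5.3 says the enrolment is enough to estimate the GS-1 accurately as a diagnostic tool. Without a stated hypothesis or an expected precision, that statement cannot be checked.

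**Working it through.** **Inputs from Protocol 5.3.** Preliminary kappa 0.34; equal marginal rates in the two modalities (value not given); 80% power; 5% type I error (sidedness not given); 94 eyes; 10–20% unreadable; 120 eyes enrolled.

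**Assumptions added here.** A two-category diagnosis, independent eyes, a two-sided test, and a common marginal rate p, first set to 50% and then varied. The value 0.20 as the floor of fair agreement, and 0.60 as a possible alternative, are not in the protocol.

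**Formula.** For a two-category kappa with common marginal p, the large-sample variance per eye is

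V(k) = (1−k)·[(1−k)(1−2k) + k(2−k)/(2p(1−p))],

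which reduces to 1−k² at p = 0.5. The number of eyes is

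n = [1.960·√V(k0) + 0.842·√V(k1)]² / (k1−k0)².

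**Trying to reproduce 94 at p = 0.5**

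- Null 0, alternative 0.34: V = 1 and 0.8844. (1.960 + 0.842×0.940)/0.34 = 8.09; squared, 65.5, so 66 eyes (52 one-sided). With 94 eyes, (0.34×√94 − 1.960)/0.940 = 1.42, which is 92% power.
- Null 0.34, alternative 0.60: V = 0.8844 and 0.64. (1.960×0.940 + 0.842×0.80)/0.26 = 9.68; squared, 93.7, so 94 eyes.
- Null 0.20, alternative 0.34: V = 0.96 and 0.8844. (1.960×0.980 + 0.842×0.940)/0.14 = 19.37; squared, 375.2, so 376 eyes (295 one-sided). With 94 eyes, (0.14×√94 − 1.960×0.980)/0.940 = −0.60, which is 27% power.

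**Varying the marginal rate**

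- Null 0, alternative 0.34, p = 8.5%: V(0.34) = 2.534. (1.960 + 0.842×1.592)/0.34 = 9.71; squared, 94.2.
- Null 0.05, alternative 0.34, p = 35%: V = 1.016 and 0.958. The result is 93.2, so 94 eyes.
- Null 0, alternative 0.34, p = 5%: 115.6, so 116 eyes.

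Several unstated combinations therefore lead to about 94. The protocol's text does not choose between them.

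**Inflation.** 94/0.9 = 104.4 and 94/0.8 = 117.5, so 105 to 118 eyes. The target of 120 covers both, and this step is sound.

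**Precision.** With 94 independent eyes and p = 0.5, the 95% half-width is 1.96×√(0.8844/94) = 0.19 at kappa 0.34, giving an interval of about 0.15 to 0.53. At kappa 0.60 it is 1.96×√(0.64/94) = 0.16. Neither allows for correlation between the two eyes of a patient.

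**Sized quantity against named analyses**

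| Place | Comparison | Quantity | Method |
|---|---|---|---|
| 5.3 | manual gonioscopy vs GS-1 | recording a diagnosis | kappa |
| 4.2, accuracy | GS-1 vs biomicroscopy and gonioscopy | angle measurement | ANOVA |
| 4.2, reproducibility | two observers of GS-1 images | angle | kappa, ICC |
| 6.7 | three modalities | Scheie and Shaffer grades | linear and quadratic models |

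No row below the first contains the quantity that was sized.

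**The case against.** A reader might infer that 94 is an arithmetic error and should be 66, or that it can only have come from testing 0.34 against 0.60. The documents support neither reading. Section 5.3 says the two modalities "have an equal probability of recording a diagnosis", which means equal marginals and not necessarily 50%. With 0 against 0.34 at a marginal of about 8.5%, a plain test against chance also gives about 94. The 0.60 is back-calculated and appears nowhere in the protocol, and the 0.20 floor is likewise brought in from outside. If 0 against 0.34 at 50% was meant, 94 errs on the safe side. This part of the objection stands: the number is unverifiable, not shown to be wrong.

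A reader might also infer that an estimate near 0.34, or significance against zero, is set to be declared validation of the device. The protocol sets no success threshold on kappa, so that would be a prediction about reporting and not something the plan states.

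Finally, a separate statistical analysis plan, or the open reference to more advanced methods in 6.7, might contain a between-modality kappa. This does not remove the mismatch. The protocol does not leave the method for comparing modalities open: section 4.2 names ANOVA for that comparison and gives kappa to the observers.

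**Conclusion.** The firm part of the point is the mismatch. The 80% power in 5.3 is for a kappa between gonioscopy and GS-1, and the analyses named in 4.2 and 6.7 do not include it. This rests on the protocol's own text and needs no outside figure.

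The second part is that 94 eyes cannot be derived from what is stated, because null, alternative, marginal rate and sidedness are missing. The size of the ambiguity is large. At 50% marginals and two-sided 5%, the three candidate hypotheses need 66, 94 and 376 eyes, and 94 eyes give 92%, 80% and 27% power respectively. These figures assume a two-category diagnosis and independent eyes. The wording about detecting fair agreement fits the 94 under some assumptions and not under others, and only the sponsor can say which were used.

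**What to change.** In 4.2 and 6.7, declare the kappa between GS-1 and conventional gonioscopy, on the scale used for sizing, as the accuracy analysis in place of the ANOVA test of similarity. Report it with a 95% CI that accounts for two eyes per patient.

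In 5.3, restate the calculation with the null kappa, alternative kappa, marginal rate and sidedness that were actually used. Then correct either the stated power or the phrase "To detect a fair agreement between the two modalities" so that the two agree. Add the expected CI half-width: about 0.19 at kappa 0.34 with 94 independent eyes and 50% marginals, to be recalculated for the sponsor's own marginal rate.

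The cost is more than wording, because the named accuracy analysis changes, and the power may look less favourable once the hypothesis is written out. Enrolment need not change: 120 eyes still covers 94 readable eyes at 20% loss, and if the restated hypothesis has less than 80% power, the protocol can say so and rely on the stated precision.

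### The protocol expects 10–20% unreadable images but counts them in no outcome, so its accuracy and reproducibility results are conditional on a readable image

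*Protocol*

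**What the plan says.** Protocol section 4.2 (Primary Outcome Variables) compares GS-1 images with ultrasound biomicroscopy and goniolens images "to determine if the NIDEK Gonioscope GS-1 can accurately and reliably capture relevant findings". It then lists the outcomes: angle measurements compared by ANOVA, inter-observer reproducibility by kappa and intraclass correlation, and time to obtain images compared by ANOVA.

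Section 5.3 (Number of Participants) is the only place that mentions unreadable images. It reports that "Cohen's Kappa of 0.34 was measured" in preliminary data and concludes that "we will need to collect data from 94 eyes". The next sentence begins "To account for the portion of images that are uninterpretable due to poor quality (10-20"%) and arrives at "a total of 120 eyes (60 participants) would be satisfactory for us to estimate the GS-1 as a diagnostic tool accurately". It does not say whether the unreadable images come from GS-1, the goniolens and slit lamp, or ultrasound.

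Sections 6.1 (Study Procedure) and 6.7 (Primary Analyses) analyse angle width as read from the images. They say nothing about an eye whose image cannot be read.

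**The concern.** An unreadable GS-1 image is a failure of capture, and capture is what section 4.2 sets out to assess. The protocol anticipates unreadable images at a rate of 10–20% and responds only by enrolling more eyes. Angle measurement, kappa and intraclass correlation exist only for an image that can be graded. Those results therefore say how well GS-1 performs once a readable image exists, and leave open how often it delivers one.

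The gap matters because the Background section presents GS-1 as a possible replacement for conventional gonioscopy, and a replacement has to work in the eyes presented to it. Section 5.4 already excludes corneal opacities and patients who cannot fixate, so the expected loss comes on top of a population in which two obstacles to imaging have been removed. Gradability is also best recorded prospectively, since section 6.3 describes a single visit.

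**Working it through.** **Inputs.** From section 5.3: 94 eyes required, 120 enrolled, 10–20% unreadable, kappa 0.34, and the assumption that "manual gonioscopy and automated gonioscopy GS-1 have an equal probability of recording a diagnosis". The value of that probability is not given. I assume 0.5 for illustration and show 0.1 as a contrast. As the protocol's own inflation does, I treat the 10–20% as a share of eyes.

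**1. Reproducing the 120.** Inflation for loss is n/(1 − d):
- d = 0.10: 94/0.90 = 104.4, so 105 eyes
- d = 0.15: 94/0.85 = 110.6, so 111 eyes
- d = 0.20: 94/0.80 = 117.5, so 118 eyes (59 participants)

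The stated 120 is the upper end with slight rounding; the exact loss it allows is 1 − 94/120 = 21.7%. The inflation is sound. It makes sense only if unreadable eyes are expected to contribute nothing to the analysis.

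**2. Eyes affected.** 0.10 × 120 = 12 and 0.20 × 120 = 24. That leaves 96 to 108 eyes analysed.

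**3. Conditional against all-attempted result (illustration).** For a two-category grade with common marginal p, chance agreement is Pe = p² + (1 − p)² and observed agreement is Po = Pe + kappa × (1 − Pe).

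| p | Pe | Po in readable eyes | Readable and agreeing, of all attempted: 10% loss | 20% loss |
|---|---|---|---|---|
| 0.5 | 0.50 | 0.50 + 0.34 × 0.50 = 0.670 | 0.670 × 0.90 = 0.603 | 0.670 × 0.80 = 0.536 |
| 0.1 | 0.82 | 0.82 + 0.34 × 0.18 = 0.881 | 0.881 × 0.90 = 0.793 | 0.881 × 0.80 = 0.705 |

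The gap is Po × d: about 7 to 13 points at p = 0.5, and about 9 to 18 points at p = 0.1.

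**4. What the lost eyes could have shown.** At p = 0.5, suppose every lost eye had been readable. If all of them disagreed, overall agreement would be 0.603 (10% loss) or 0.536 (20% loss). If all agreed, it would be 0.603 + 0.10 = 0.703 or 0.536 + 0.20 = 0.736. Both ranges contain 0.67, so the documents fix neither the size nor the sign of a bias in the readable-only figure.

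**5. Can the planned size estimate the failure rate?** At 15%, the 95% half-width is 1.96 × √(0.15 × 0.85/120) = 0.064 if eyes are independent. With two eyes per patient the variance grows by at most a factor of 2 (perfect correlation within patient), giving 0.064 × √2 = 0.090. So the half-width is about 6 points, and at most about 9. Wilson intervals with independent eyes are 5.8–16.7% for 12/120 and 13.8–28.0% for 24/120.

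**The case against.** The strongest reply is that handling of unreadable images belongs in a statistical analysis plan, which is not at hand. An allowance in the sample size does not decide how such images are analysed or reported, and kappa among readable pairs answers a legitimate question. Much of this stands. Exclusion is implied by the step from 94 to 120 and nowhere stated, and a later plan could add a rule. But the protocol itself fixes the outcome list, and that list omits capture failure while naming capture as the aim.

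Several stronger readings are tempting and are not supported:
- **That the 10–20% are GS-1 failures.** Section 5.3 names no modality. Goniolens and ultrasound images could account for some or all of them.
- **That the readable-only statistics favour GS-1.** The documents do not describe how unreadable eyes differ, and step 4 shows that either direction is possible.
- **That acquisition time is biased.** Section 4.2 compares the time to obtain images, and nothing excludes time spent on an image later judged unreadable.
- **That the trial could never report a failure rate.** Images are stored and read, so unreadable ones can be counted. The protocol simply does not make this an outcome.
- **That every ungradable pair should count as disagreement.** This would charge GS-1 with failures of the comparator image.

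**Conclusion.** The point holds as an inconsistency between the aim and outcome list in section 4.2 and the expectation in section 5.3. Some 12 to 24 of 120 eyes are implied to leave the analysis, and no outcome records why or for which modality. The planned accuracy and reproducibility results remain valid as statements conditional on a readable image; alone they do not show whether GS-1 captures findings reliably in the eyes attempted.

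The figures of 67% against 54–60% illustrate scale. They rest on the protocol's kappa of 0.34, an assumed marginal of 0.5, a two-category grade, and loss counted per eye. They describe eyes with a readable, agreeing pair and do not attribute the loss to GS-1. The sample size inflation is not at fault.

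**What to change.** - Record gradable yes/no for every image in each modality. Keep an image not taken separate from one taken but unreadable, because section 6.1 says only that images may be obtained.
- Add the ungradable proportion by modality to the outcomes in section 4.2, with a 95% confidence interval clustered by patient and a paired comparison of GS-1 with goniolens images.
- Keep the kappa and intraclass correlation among readable images, labelled as conditional on a readable image.
- Beside them, report the proportion of eyes with a readable goniolens image in which GS-1 gives a readable and agreeing grade. Comparator failures are then not charged to GS-1. In the illustration at p = 0.5, this figure would be 54–60% if all the loss came from GS-1 and 67% if all of it came from the goniolens.

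The cost is one data field per image and a short protocol amendment. No extra patients, readers or procedures are needed. The drawback for the sponsor is a headline figure that will look less favourable to the extent that GS-1 images prove unreadable.
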